### Tissue and Vascular Morphology

Tissue injury is evaluated using histopathological analysis before and after ex vivo organ perfusion. Biopsy samples are taken during organ retrieval to assess graft suitability, after graft reperfusion into the recipient, and at the end of the transplant. Pretransplant biopsies are obtained according to our center practice. All tissue samples are sent to Bologna Transplant Center to reduce interlaboratory bias in preparing the slides.

For the livers, parenchymal and vascular damage are evaluated. For the kidneys, glomerular, vascular, tubular, and parenchymal damage are evaluated. Tissue samples are examined by two double-blind pathologists, who grade any damage from moderate to severe.

In addition, we perform immunohistochemical assays to investigate endothelial and epithelial cell injury, ischemia- reperfusion damage, the pro-inflammatory and anti- inflammatory environment, growth factors, dedifferentiation, repair, and apoptosis using specific stainings. Electron microscopy is performed to assess the features of oxidative injury, focusing on preservation of epithelial mitochondria, endothelial cells of the glomerular and peritubular capillaries, and liver sinusoids.

Tissue and perfusate samples are collected and coded to guarantee privacy and data protection in accordance with EU regulations. Perfusate and tissues samples collected for RT-PCR are snap-frozen and stored at –80°C. Tissue collected for immunohistochemical assays are preserved in glutaraldehyde solution.

### Posttransplant Follow-up

Postoperative follow-up is carried out according to the local protocol. Hepatic and renal function tests and abdominal ultrasound are performed at each follow-up visit. Follow-up will end at 12 months.

### Risk Analyses

Technical assistance by a team of expert technicians is provided during all phases of the machine perfusion procedures.

Vascular endothelial damage is avoided by perfusing the liver solely through the portal vein, leaving the hepatic artery untouched, and keeping the perfusion pressure of the renal artery and portal vein at low levels, which we previously demonstrated as being safe in preclinical and clinical studies [7,8].

### Data Management

Demographic, clinical, and biological data of donors and recipients are collected and prospectively entered in the database. The data registration is anonymous, and a study identification code is assigned to each transplant, in accordance with the Helsinki Declaration.

Missing values are handled properly by the researchers to achieve accurate inferences about the data during the analyses of the results.

### Statistical Analyses

#### Sample Size Calculation

The sample size was calculated using the primary outcomes of EAD and DGF for LT and KT, respectively, and the secondary outcomes of PNF and LHS, as reported in similar studies [11,19,20].

In particular, the rates of PNF and EAD are expected to decrease for the LT-HOPE group, thereby improving the postoperative course and LHS. We are expecting the following reductions in these parameters: PNF, 5% (HOPE) vs 10% (SCS); EAD, 10% (HOPE) vs 20% (SCS); and postoperative LHS <21 days, 80% (HOPE) vs 50% (SCS).

In KT, HOPE should reduce the rate of DGF from 50% to 30%, with a general improvement in the postintervention outcomes.

Based on these parameters, the total sample size was estimated at 220 patients, with distribution throughout the 4 groups as already explained (alpha=.05, two-sided test, power of 80%; calculated with nQuery Advisor 7.0, Statsols, Cork, Ireland).

The sample size was calculated to account for a dropout risk of 5-10% for the year.

A preliminary analysis will be performed when half of the enrollment is completed.

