## Methods

### Study Design

In an open-label, single-center, randomized clinical trial, we will compare HOPE (study group) to SCS (control group) in ECD KT and LT. In the HOPE group, 55 livers and 55 kidneys will be preserved by SCS at 4-10°C from the end of organ retrieval until arrival at the transplant hospital. Afterwards, grafts are preserved with HOPE at 4-10°C for a minimum of 1 hour for livers and 2 hours for kidneys until implantation in the recipient. HOPE starts during back-table graft preparation. During the back-table procedure, organs are flushed with a preservation fluid (Belzer solution). Then, the organ is perfused with HOPE through a closed recirculating system.

In the SCS group, 55 livers and 55 kidneys will be preserved by SCS at 4-10°C from the end of the organ retrieval until implantation in the recipient.

In this study, 220 patients will be enrolled, with 55 in each of the following groups: LT-HOPE, LT-SCS, KT-HOPE, and KT-SCS.

The trial design is outlined in Table 1, and the protocol algorithm is shown in Figure 1.

Based on the number of transplants usually performed at the participating center, this clinical study is estimated to be accomplished in 2 years, including 12 months of patient enrollment and 12 months of follow-up. Enrollment at the Bologna Transplant Center started in January 2019 and will end in January 2020 (Figure 2).

**Table 1 table1:** Trial design to evaluate the benefit of end-ischemic hypothermic oxygenated perfusion (HOPE) on extended criteria donor grafts for livers and kidneys as compared with static cold storage (SCS), N=220.

			Study group (HOPE)		Control group (SCS)
Number of livers			55		55
Number of kidneys			55		55

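### With 55 per arm, power is about 31% for EAD and 57% for DGF, not the stated 80%

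*Protocol article*

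**What the plan says.** The Sample Size Calculation section bases the size on both primary outcomes and two secondary ones: "The sample size was calculated using the primary outcomes of EAD and DGF for LT and KT, respectively, and the secondary outcomes of PNF and" length of hospital stay (LHS). It then gives the assumed rates:

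- Liver, primary: "EAD, 10% (HOPE) vs 20% (SCS").
- Kidney, primary: "In KT, HOPE should reduce the rate of DGF from 50% to 30" percent.
- Liver, secondary: primary non-function (PNF) 5% vs 10%, and LHS under 21 days 80% vs 50%, HOPE first in each pair.

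From these it concludes that "the total sample size was estimated at 220 patients, with distribution throughout the 4 groups as already explained (alpha=.05, two-sided test, power of 80" percent). On losses it adds: "The sample size was calculated to account for a dropout risk of 5-10% for the year".

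The Study Design section fixes the split of the 220 patients, "with 55 in each of the following groups: LT-HOPE, LT-SCS, KT-HOPE, and KT-SCS". Randomization is 1:1, and the Statistical Tests section plans chi-squared tests for categorical variables with P<.05 as the criterion.

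**The concern.** EAD is defined only for liver recipients and DGF only for kidney recipients. Each primary outcome is therefore tested on 55 vs 55, not on 220 patients. Halving a 20% event rate cannot usually be shown at 80% power with 55 per arm, and a fall from 50% to 30% normally needs over 90 per arm. The article supplies every input (rates, alpha, sidedness, allocation, group size, test), so the result can be checked, and it does not follow from them.

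The power label governs how a null result is read. A non-significant EAD or DGF comparison from a trial described as having 80% power invites the conclusion that HOPE does not help. At the power actually available, such a result would be common even if the planned effects were real.

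**Working it through.** **Inputs.** Two-sided alpha .05 (z = 1.960), target power 80% (z = 0.842), n = 55 per arm, and the rates above, all from the Sample Size Calculation and Study Design sections.

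**Formulas** (two proportions, 1:1, pooled variance under the null). With d = |p1 − p2|, p̄ = (p1 + p2)/2, s0 = √[2p̄(1 − p̄)] and s1 = √[p1(1 − p1) + p2(1 − p2)]:

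- power = Φ[(d√n − 1.960·s0)/s1]
- n per arm for 80% = (1.960·s0 + 0.842·s1)²/d²

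**Attempt to reproduce the stated 80% at 55 per arm.**

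- *EAD, 20% vs 10%*: d√55 = 0.742, s0 = 0.505, s1 = 0.500. z = (0.742 − 0.990)/0.500 = −0.496, so power is **31.0%**. n for 80% = (0.990 + 0.421)²/0.01, or **199 per arm**.
- *DGF, 50% vs 30%*: d√55 = 1.483, s0 = 0.693, s1 = 0.678. z = (1.483 − 1.358)/0.678 = 0.185, so power is **57.3%**. n for 80% = (1.358 + 0.571)²/0.04, or **93 per arm**.

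| Contrast | Power at 55 per arm | Exact power, uncorrected chi-squared | n per arm for 80% | With continuity correction |
|---|---|---|---|---|
| EAD 20% vs 10% (primary) | 31.0% | 31.1% | 199 | 219 |
| DGF 50% vs 30% (primary) | 57.3% | 57.6% | 93 | 103 |
| PNF 10% vs 5% (secondary) | 16.6% | 15.9% | 435 | 474 |
| LHS <21 days 50% vs 80% (secondary) | 92.1% | 92.6% | 39 | 45 |

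The stated 80% is not reproduced for either primary outcome. Only LHS exceeds it.

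**Other calculation choices, EAD and DGF at 55 per arm.**

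- Unpooled variance: 31.7% and 59.0%.
- Fisher exact or continuity-corrected test: about 22% and 49%.
- One-sided .05, contrary to the text: 42.9% and 69.4%.

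**Dropout.** If 55 already includes a loss allowance, the evaluable number is smaller. At 50 per arm (about 10% lost), power is 28.6% for EAD and 53.3% for DGF. Inflating the required numbers by n/(1 − d) for 5–10% dropout gives 210–222 per arm for EAD and 98–104 for DGF.

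**Detectable effects.** Solving the power formula at 55 per arm for 80%, EAD must fall from 20% to about 3.1%, or DGF from 50% to about 24.5%.

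**Precision.** The expected 95% CI half-width for the risk difference is 1.96·s1/√55:

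- EAD: 1.96 × 0.500/7.416 = 0.132, about 13 points against a planned effect of 10.
- DGF: 1.96 × 0.678/7.416 = 0.179, about 18 points against a planned effect of 20.

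**The case against.** The core arithmetic is hard to contest, but several points deserve an answer.

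- **Dropout timing.** The 5–10% is stated for the year, while EAD and DGF are both read in the first postoperative week and randomization follows organ acceptance. One-year losses need not remove 10% of week-1 outcomes. This stands: the figures at 50 per arm are a sensitivity case, and 31% and 57% are the main figures. It does not help the claim, because a size said to include a loss allowance should exceed the required n, and 55 is below it for both outcomes.
- **L-GrAFT.** The Liver Transplant Primary Outcome section also names this score. No effect size is given, so its power cannot be computed. The finding therefore covers the two primary outcomes the article says it sized on.
- **Paired kidneys.** The Randomization section puts kidneys from one donor into opposite arms when both come to the center, so some DGF outcomes may be correlated, whereas 57% assumes independence. A paired analysis could gain power, but the stated test is an unpaired chi-squared and the number of pairs is not given. Even if all 110 kidneys formed 55 complete pairs, an approximate McNemar calculation needs a within-pair correlation near 0.45 (assumed). The covariance is then 0.45 × √(0.25 × 0.21) = 0.103, the variance of the difference is 0.46 − 0.206 = 0.254, and the discordant proportion is 0.254 + 0.04 = 0.294. So z = (1.483 − 1.960 × 0.542)/0.504 = 0.83, or about 80%. This cannot help EAD.
- **Pooling organs.** No pooled primary analysis is stated. At 110 vs 110, a 20% vs 10% contrast gives 55%, and the average of the two organs' rates (35% vs 20%) gives about 71%.
- **Origin of 55.** LHS is the only listed contrast that 55 per arm satisfies, which suggests it drove the size. However, LHS needs 39 per arm, 45 with continuity correction and 50 after 10% dropout, none of which is 55. The origin is not stated, and the finding does not depend on it.
- **Reporting remedy.** How to present intervals and read a null result is often left to an analysis plan. That is fair as a general rule, but once the power statement is corrected, the reading of a non-significant result should be fixed alongside it.

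**Conclusion.** The power statement is wrong as written and must be corrected. On the article's own rates, alpha, sidedness and group size, the design gives about 31% power for EAD and 57% for DGF. The required numbers are about 3.6 times (199/55) and 1.7 times (93/55) those planned. If the planned effects are real, the chance of missing them is about 69% in livers and 43% in kidneys.

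These figures assume independent binomial outcomes, an uncorrected chi-squared test, full week-1 data and no pooling across organs. Fisher's test or losses would lower them. No standard choice of variance, correction or sidedness brings either outcome to 80% at 55 per arm. A later analysis plan cannot change this, because the fault lies in a stated result and not in an omitted detail.

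**What to change.** In the Sample Size Calculation section:

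1. Replace the 80% statement with the delivered power at 55 per arm: about 31% for EAD (20% vs 10%) and 57% for DGF (50% vs 30%). Add 29% and 53% at 50 per arm, labelled as a sensitivity case for 10% loss.
2. State that, of the listed contrasts, only LHS under 21 days exceeds 80% (about 92%), and that no power is claimed for L-GrAFT.
3. Give the effects detectable at 80% power: EAD 20% to about 3%, DGF 50% to about 24.5%.
4. Make the risk difference with its 95% CI the headline result for each organ (expected half-widths about 13 and 18 points), and state that P of .05 or more will not be read as absence of benefit.

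The cost is a few sentences and a less favorable power statement. No patients are added and nothing clinical changes. The correction makes the statement true but does not raise the power: reaching 80% on both outcomes would take 398 livers and 186 kidneys (2 × 199 and 2 × 93), 584 in all before dropout.

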#### Preliminary Analyses

To monitor and optimize the planned surgical and clinical procedures, real-time data analyses are performed before the final data collection. In detail, we are performing two interim analyses on the data from the first 7 posttransplant days. The primary analyses will be performed after the enrollment of 60 patients. The second analyses will be performed after the enrollment of 160 patients.

#### Statistical Tests

The continuous variables will be compared using parametric (ANOVA) or non-parametric (Kruskal-Wallis) tests according to the data distribution, and the categorical variables will be compared using chi-squared tests. Multivariate analysis will be performed using forward stepwise logistic regression analysis. Survival analysis will be conducted using the Kaplan-Meier method. *P* values <.05 will be considered statistically significant.

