#### Randomization

Patients are randomized 1:1 to the HOPE and SCS groups according to the treatment list produced by the randomizer tool. For KT, patients are stratified according to the duration of CIT before HOPE starts (longer or shorter than 12 hours); grafts with CIT >20 hours are excluded from the study. For LT, patients are stratified according to the contemporary presence of ECD liver criteria (more or less than 5 criteria). The study information and informed consent form are distributed to potential recipients. Randomization is performed for patients who sign the consent form after the organ is deemed suitable for transplantation.

To favor comparison between paired kidneys, when both kidneys from the same donor are allocated to the same center, grafts are automatically assigned to a study group and the corresponding control group. Furthermore, in cases where there are multiple transplants occurring at the same time, we prioritize LT over KT, to reduce the CIT.

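### Chi-squared for all categorical variables ignores the order of the histology damage grades and does not secure use of the retrieval-biopsy grade (minor, supportive analysis)

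*Protocol article*

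**What the plan says.** The Statistical Tests section assigns methods by type of variable. For categorical data, "the categorical variables will be compared using chi-squared tests". For continuous data, "The continuous variables will be compared using parametric (ANOVA) or non-parametric (Kruskal-Wallis) tests according to the data distribution". It adds that "Multivariate analysis will be performed using forward stepwise logistic regression analysis", without naming outcomes or covariates.

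The Tissue and Vascular Morphology section describes the histology reading: "Tissue samples are examined by two double-blind pathologists, who grade any damage from moderate to severe". On timing it says that "Biopsy samples are taken during organ retrieval to assess graft suitability, after graft reperfusion into the recipient, and at the end of the transplant", and also that "Pretransplant biopsies are obtained according to our center practice". The number of grade levels is not given.

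Under Randomization, "Randomization is performed for patients who sign the consent form after the organ is deemed suitable for transplantation". Organ Retrieval keeps organs on ice while the biopsy is analysed and until eligibility is finally decided. A retrieval grade, where one exists, therefore precedes allocation.

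The abstract's Methods list histologic findings among what is evaluated in each group. The primary and secondary outcome sections for liver and kidney do not list them.

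**The concern.** A damage grade is ordered categorical data, and the only rule stated for categorical data is a test that treats the levels as interchangeable labels. The study hypothesis has a direction: HOPE should leave less tissue damage. For such a shift, an unordered test spreads its sensitivity over patterns that nobody expects.

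Extended-criteria grafts also differ in damage before preservation starts. The retrieval grade cannot be affected by the arm, so it is a legitimate covariate, yet nothing in the section secures its use.

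The trial is open-label, and the pathologists' reading is the only assessment that the article describes as blinded. What is at stake is the sensitivity of that supportive evidence. The validity of the test is not in question.

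**Working it through.** **Inputs.** From the article: 55 grafts per organ-by-arm group, 1:1 allocation, two-sided alpha .05. The article gives no histology effect, grade distribution, number of levels or power, so there is no stated figure to reproduce. Everything else below is an assumption.

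**Step 1: cost of ignoring order.** Let the SCS grades follow probabilities p. Shift HOPE toward less damage by a common odds ratio OR, so that odds(grade ≤ k) under HOPE = OR × odds(grade ≤ k) under SCS. Power was simulated with 5,000 trials per setting for the Pearson chi-squared (levels − 1 df) and a midrank Wilcoxon-type test (1 df).

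| SCS grades (%) | OR 2: chi-sq / ordered | OR 2.5 | OR 3 |
|---|---|---|---|
| 60/40 | 40 / 40 | 58 / 58 | 72 / 72 |
| 30/40/30 | 40 / 49 | 63 / 73 | 79 / 86 |
| 50/30/20 | 35 / 45 | 56 / 66 | 71 / 80 |
| 25/25/25/25 | 36 / 52 | 57 / 75 | 76 / 88 |
| 40/30/20/10 | 33 / 49 | 54 / 71 | 70 / 84 |

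With three or four levels the unrounded gaps run from 7.4 points (78.6 vs 86.0) to 17.2 points (53.9 vs 71.1). With two levels there is no gap.

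**Step 2: analytic check of one row.** Take 30/40/30 and OR 2.
- First cut: odds 0.30/0.70 = 0.429, doubled 0.857, cumulative 0.4615.
- Second cut: odds 0.70/0.30 = 2.333, doubled 4.667, cumulative 0.8235.
- HOPE grades are therefore 46.2/36.2/17.6%.

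The Pearson noncentrality is n × Σ(p − q)²/(p + q) = 55 × (0.1615²/0.7615 + 0.0380²/0.7620 + 0.1235²/0.4765) = 55 × 0.0682 = 3.75. On 2 df (critical value 5.99) this gives 39% power. Computed in the same way, the midrank test's noncentrality is also 3.75, but on 1 df (critical value 3.84), which gives 49%. The signal is the same in both tests, and the loss is the price of the extra degree of freedom.

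**Step 3: value of the baseline grade.** Three levels cut at latent ±0.52 (about 30/40/30), HOPE shifted by 0.5 SD, 3,000 trials per setting. The adjusted analysis is a rank analysis of covariance on the retrieval grade.

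| Latent correlation, retrieval vs later grade | Chi-sq | Ordered | Ordered + baseline |
|---|---|---|---|
| 0 | 53.7% | 64.2% | 63.5% |
| 0.3 | 53.7% | 64.9% | 66.8% |
| 0.5 | 53.7% | 64.2% | 70.9% |
| 0.7 | 53.4% | 64.8% | 81.8% |

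The gain from adjustment is about 0, 2, 7 and 17 points. For a two-level grade split at the median, adjustment moves power from 53.5 to 53.4%, 54.7 to 56.3%, 52.3 to 57.9% and 54.4 to 64.3%, a gain of about 0 to 10 points over chi-squared. With no effect, rejection rates in this step were 4.0 to 6.2% for all methods, so none is invalid.

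**Step 4: where chi-squared wins.** For a non-monotone difference, 30/40/30 vs 15/70/15%, chi-squared has 83% power and the ordered test 6%.

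**The case against.** The strongest reply is that the rule is a generic sentence in a condensed article. It does not name histology, and Kruskal-Wallis, which is a Wilcoxon-type test with two arms, stands in the same section. That softens the point but does not remove it. Kruskal-Wallis is tied to continuous variables, and the categorical rule is stated without exception.

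Four stronger readings are tempting, and the documents do not support them:

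- *The scale is none, moderate, severe.* Grading any damage suggests that some samples show none, but only two anchors are named. If there are just two levels, the ordering argument falls away.
- *Every graft has a baseline grade.* Pretransplant biopsies follow centre practice, and no text says that each graft is biopsied.
- *The analysis is purely unadjusted.* A multivariable logistic model is planned, and "Tissue injury is evaluated using histopathological analysis before and after ex vivo organ perfusion", so some before-and-after comparison is contemplated. However, stepwise selection need not retain the baseline grade, and ordinary logistic regression would require a multi-level grade to be dichotomised. SCS grafts have no ex vivo perfusion, so the before-and-after reading does not define a between-arm comparison.
- *Chi-squared has no advantage.* Step 4 shows that it has one, although for a pattern that the study does not hypothesise.

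It is also fair that baseline adjustment gains little at a correlation of 0.3 or below, and that chance imbalance under randomization costs precision without inflating the false-positive rate.

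**Conclusion.** The point holds in conditional form. The stated rule uses neither the order of the damage grades nor, with any certainty, the pre-randomization retrieval grade. With three or more levels and a one-directional shift, ignoring order costs about 7 to 17 points of power at 55 per arm. Using the baseline adds about 0 to 17 points for latent correlations from 0 to 0.7. With two levels only the baseline gain remains. These sizes rest on assumed grade distributions, odds ratios of 2 to 3 (a 0.5 SD latent shift in the baseline runs) and assumed correlations.

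A reader might infer that the trial's main conclusions are weakened. They are not: EAD and DGF are binary, the sample size does not rest on histology, and histology is not a listed outcome. Priority: minor.

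**What to change.** In Statistical Tests, except ordered grades from the chi-squared rule and state the number of levels. Compare the post-reperfusion damage grade between HOPE and SCS, separately for liver and kidney, with a proportional-odds model or rank analysis of covariance; use logistic regression if the grade has two levels. Include the same graft's retrieval grade as a fixed covariate where it exists, with a missing-baseline category where it does not. For kidneys, account for donor pairs, because the Randomization section assigns two kidneys from one donor to opposite arms. Keep chi-squared for unordered variables.

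The cost is one or two sentences, with no new biopsies or readings. The drawbacks are lower sensitivity to non-monotone differences and incomplete baselines for some grafts.
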